### Data collection and management

Table 1 gives an overview of the data to be collected and the time of acquisition, including routinely gathered data such as demographics (age, gender, weight, body mass index), severity of illness (Acute Physiology and Chronic Health Evaluation (APACHE) II score, Therapeutic Intervention Scoring System (TISS28 und TISS76), Sequential Organ Failure Assessment (SOFA) score, diagnostic data as well as laboratory findings and dose and type of sedation, relaxants, vasopressors, opiates, steroids and insulin.

All study data will be collected anonymously with an individually allocated study number on all case report forms and will be managed using REDCap (Research Electronic Data Capture) electronic data capture tools, which is a secure, web-based application designed to support data capture for research studies [46]. Vital parameters for the safety analysis will be collected by the aforementioned PDMS, which allows for continuous data collection and off-line analysis.

### Statistical analysis

Study data will be analysed as randomised with SPSS (IBM SPSS Statistics Version 21) by both intention-to-treat (main analysis) and per-protocol analysis. However, the intention-to-treat analysis will only include participants with an informed consent, as adjusted in the sample size calculation. The level of significance will be set at *p* < 0.05. Descriptive statistics will be used to describe mean outcomes and distribution. Subsequently, the outcome parameters between the two groups will be compared using Student’s *t* tests for normally distributed data and the Mann-Whitney *U* test for nonnormal distribution. For repetitive data repeated measures analysis of variance (ANOVA) will be deployed and for correlations between variables the Spearman correlation coefficients or similar will be used. If missing data are more than 5 %, multiple imputations will be performed. There will be one planned interim analysis after enrolment of 35 patients for assessment of safety.

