### Study duration

The study intervention will take place during the entire ICU stay as well as during potential readmissions to the ICU. Therefore, the study duration will be variable for each patient. After ICU discharge both groups will receive the usual physiotherapy treatment and, if necessary, rehabilitation. Likewise, there will be no difference for participants of both groups in terms of medical attention, treatment and care during the whole study duration. The study will finish with a follow-up 6 months after hospital discharge.

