### Recruitment, randomisation and blinding

Patients will be screened daily after their ICU admission for study eligibility by the physiotherapist and research nurse in charge and will be included after consultation with the responsible clinician. Reasons for nonrecruitment will be noted in a daily screening log. If a patient is considered eligible a nonparticipating doctor will reexamine the inclusion and exclusion criteria in order to safeguard the patients’ interests according to Swiss law on nonresponsive patients. Participants will then be randomised at a 1:1 ratio to either the experimental or control group by the responsible research nurse using sequentially numbered, opaque, sealed envelopes to ensure a concealed allocation [43]. The allocation sequence was generated in advance by a study nurse using unrestrictive computer-generated randomisation. Furthermore, according to the recommendations of Good Clinical Practice (GCP) the willingness to participate will be obtained in the form of a presumed consent from the patients’ proxy within 72 h (Table 1). After regaining the power of judgement, patients will be informed of the study in writing and asked retrospectively by a GCP-trained physician to provide written informed consent. Participants have the right to withdraw from the trial at any given time. If unwilling to participate or withdrawing from the trial, patients will be excluded from the study and asked if the data that has already been collected may be retained. The sample size will be adjusted for dropouts.

Due to the nature of the intervention it is not possible to maintain blinding for the treating physiotherapists, ICU staff or participants. However, the group of physiotherapists who will assess the main outcomes will be distinct from the treating therapists and will, therefore, be blinded to group allocation.

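### The main analysis is labelled intention-to-treat but is limited to patients with informed consent, and the patient's own consent is sought only after randomisation, unblinded

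*Protocol article*

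**What the plan says.** All references are to the protocol article.

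- **Statistical analysis.** Data are to be analysed according to randomisation, "by both intention-to-treat (main analysis) and per-protocol analysis". The next sentence restricts the main set: "the intention-to-treat analysis will only include participants with an informed consent, as adjusted in the sample size calculation".
- **Recruitment, randomisation and blinding.** Before or around allocation there is a check by a doctor outside the study, and "the willingness to participate will be obtained in the form of a presumed consent from the patients’ proxy within 72 h". The patient's own decision comes later: "After regaining the power of judgement, patients will be informed of the study in writing and asked retrospectively by a GCP-trained physician". For those who decline or withdraw, "patients will be excluded from the study and asked if the data that has already been collected may be retained". On masking, "it is not possible to maintain blinding for the treating physiotherapists, ICU staff or participants".
- **Study duration.** "The study intervention will take place during the entire ICU stay as well as during potential readmissions to the ICU".
- **Sample size.** A dropout rate of 15% is assumed and 15 patients are added, for a total of 115. Dropouts are glossed there as refused consent, and the ethics committee has allowed further recruitment to replace them.
- **Table 1.** Informed consent by proxy is listed, within 72 h, in the allocation column.

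**The concern.** Intention-to-treat keeps the arms comparable because membership of the analysis set is settled at randomisation. Here it is settled later, by the patient's own decision. By then the patient may have had days or weeks of the allocated physiotherapy, knows which kind it was, and has recovered to some degree. Each of these could affect willingness to sign. If refusal depends on arm and is also related to walking ability or independence, the consenting patients in the two arms are no longer like with like, and both primary outcomes are exposed.

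Two gaps in wording add to this. Refusers and withdrawers are asked whether their data may be kept, yet the analysis rule as written leaves them out whatever they answer, and nothing says what the retained data are for. Nor does the rule say whose consent counts, so the status of patients who die or never regain judgement, for whom only a proxy could agree, is open.

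**Working it through.** **1. The plan's own figures.** Inputs from Sample size: difference 54 m, SD 81 m, power 80%, alpha 0.05 (two-sided reproduces the result).

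n per arm = 2 × (1.96 + 0.84)² × (81/54)² = 2 × 7.85 × 2.25 = 35.3, rounded up to 36, or 72 in total. This agrees with the article.

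36 + 14 = 50 per arm, 100 in total. 100 + 15 = 115. Share of randomised patients expected to be lost: 15/115 = 13.0%.

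**2. What the 15 extra patients do.** With 50 per arm analysed, power at 54 m is 91.5% (normal approximation). With all 115 analysed (57.5 per arm) it would be 94.7%. The inflation therefore looks after precision. It has no bearing on which patients remain in each arm.

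**3. Form of the bias.** Let f be the fraction excluded in an arm, and D the mean of included minus excluded patients in that arm, had all been measured. The analysed mean exceeds the mean of all randomised patients by f × D, so

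bias = f_E × D_E − f_C × D_C,

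with E experimental and C control. With a common D this is D × (f_E − f_C). It is zero if D is zero in both arms, or if f and D are the same in both.

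**4. Illustration.** The article gives neither f by arm nor D. Both are assumptions here: refusers would walk 54 to 100 m less than consenters, and refusal differs by arm as shown. Reversing the arms reverses the sign.

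| Refusal in the two arms | Gap 54 m | Gap 100 m |
|---|---|---|
| 10% and 20% | 54 × 0.10 = 5.4 m (10% of 54 m) | 100 × 0.10 = 10 m (19%) |
| 5% and 25% | 54 × 0.20 = 10.8 m (20%) | 100 × 0.20 = 20 m (37%) |

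Both splits average 15%, the article's assumed rate, which is about 17 of 115 patients (0.15 × 115 = 17.25), not 15. The standard error with 50 per arm is 81 × √(2/50) = 16.2 m, so 5.4 m is one third of a standard error and 20 m is about 1.2.

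**5. Cross-check with exactly 15 exclusions.** Here 57.5 patients are randomised per arm, and D is assumed to be 0.5 to 1 SD (40.5 to 81 m). Type I error is by normal approximation with SD 81.

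| Exclusions E/C | Bias | Share of 54 m | Type I error |
|---|---|---|---|
| 7.5/7.5, same D | 0 m | 0% | 5.0% |
| 10/5 | 3.5 to 7.0 m | 7 to 13% | 5.5 to 7.2% |
| 12/3 | 6.3 to 12.7 m | 12 to 23% | 6.8 to 12.2% |
| 15/0 | 10.6 to 21.1 m | 20 to 39% | 9.9 to 25.2% |
| 7.5/7.5, D of opposite sign | 10.6 to 21.1 m | 20 to 39% | 10.0 to 25.7% |

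The last row shows that equal refusal counts would not by themselves prove the absence of bias. The 15/0 row is an extreme.

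**6. The passages side by side.** The recruitment section foresees that some refusers and withdrawers will let their data be kept. The analysis section admits only those with informed consent. Table 1 treats proxy agreement as a form of informed consent, and the analysis section does not say whether that suffices. These statements do not give one definite analysis set.

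**The case against.** The case on the other side is substantial, and parts of it stand.

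- **Consent after recovery of capacity belongs to an ethics-approved design, and data that a patient refuses to release may have to go.** This stands. The criticism is of the label, and of exclusions beyond what is required.
- **The restriction is openly stated and allowed for in the sample size.** True, but the allowance covers numbers only. Blinded assessors likewise protect measurement, not selection at the consent stage, and the multiple-imputation rule cannot reach patients already removed from the set.
- **A detailed definition of the analysis set may sit in a fuller document.** Possibly. But the article does not leave the matter open: it fixes a rule for the main analysis and names it intention-to-treat.
- **Including refusers recovers little.** This largely stands. Both primary outcomes are measured at hospital discharge. A patient who refuses before then has no discharge value to retain, and neither has one who died. Including them turns an exclusion into a missing outcome, which must be handled.

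Three stronger readings are tempting, and the documents do not support them. A reader might infer that the main set is selected on survival, because those who die cannot sign. Table 1 lists informed consent by proxy, and the sample size section describes dropouts as refusals, so this is an ambiguity and not a stated rule. A reader might infer that the safety counts are biased too. The restriction is attached to the intention-to-treat analysis, the Safety section records and reports adverse events without a consent condition, and the interim safety analysis is triggered by enrolment. Finally, a reader might take the metre figures as estimates. They follow wholly from assumed gaps and splits.

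**Conclusion.** The point holds as a defect in the stated main analysis set. An analysis described as following randomisation and as intention-to-treat is conditioned on consent. The patient's own consent is sought after randomisation, without blinding, and at a time when allocation and recovery could influence it. Planned losses are 15 of 115 patients (13%), and replacing them does not restore comparability.

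Whether bias results, and in which direction, cannot be known from the article. The range runs from zero, if refusal is unrelated to arm and outcome, to about 5 to 20 m on the 6-Minute Walk Test under the assumptions in step 4. The cross-check with 15 exclusions gives 0 to about 21 m. The effect on the Functional Independence Measure is not sized, because the article gives no figures for it. The treatment of patients who allow retention, and of patients with proxy consent only, is unsettled and must be reconciled between the recruitment section, Table 1 and the analysis section.

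**What to change.** 1. **Define the main set** as all randomised patients whose data may lawfully be used, in the arm allocated. Name the groups that this includes: patients who consented; patients with proxy consent who died or never regained judgement; and refusers or withdrawers who allow collected data to be retained.
2. **Exclude only patients whose data must be deleted.** If there are any, call the set modified intention-to-treat.
3. **Report these exclusions by arm**, with number and timing relative to randomisation, in the participant flow.
4. **State how missing discharge outcomes are handled**, with deaths treated separately from refusals before discharge, since neither has a discharge walk distance or independence score. Say whether the existing rule of imputing above 5% missing applies to each.
5. **Add a sensitivity analysis** for excluded and missing patients. For those whose data are deleted, the observed exclusion fractions can be put into f_E × D_E − f_C × D_C, with D varied separately by arm, to show what gap would change the conclusion.

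The cost is analysis-set wording that can be settled before the data are analysed, one reporting row by arm, and a little more analysis work. No data are needed beyond those that patients are already asked to let the trial keep. The price is more missing outcomes in the main set, and so more reliance on how they are handled.

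### The primary analysis leaves the effect measure to the observed distribution and makes no use of baseline data already collected; one prespecified adjusted model would be a low-cost gain in precision and prespecification

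*Protocol article*

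**What the plan says.** **Test.** The Statistical analysis section sets the order of work: the outcomes and their distribution are described first, after which "the outcome parameters between the two groups will be compared using" Student's t "tests for normally distributed data and the Mann-Whitney" U test for non-normal data. This is the only between-group comparison given for single-time-point outcomes, so it governs both primary outcomes, the 6MWT and the FIM at hospital discharge. Repeated measures ANOVA is kept for repeated data. The section states no covariate.

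**Randomisation.** Under Recruitment, randomisation and blinding: "Participants will then be randomised at a 1:1 ratio to either the experimental or control group", and "The allocation sequence was generated in advance by a study nurse using unrestrictive computer-generated randomisation". The natural reading is simple randomisation, without blocks or strata.

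**Baseline data.** Data collection and management lists "demographics (age, gender, weight, body mass index") and "severity of illness (Acute Physiology and Chronic Health Evaluation (APACHE) II score"; Table 1 schedules APACHE II at ICU admission and demographic data at allocation.

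**Target difference.** The Sample size section rests on a 54 m difference in 6MWT with SD 81 m.

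**The concern.** There are two linked weaknesses.

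1. The sample size is built on a difference in mean walking distance. If the data look non-normal, the comparison becomes one of ranks, which does not estimate that difference. The switch is a realistic prospect: walking distance cannot fall below zero and the FIM is a bounded score. What the trial estimates would then be known only once the outcome data have been examined.

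2. Simple randomisation does nothing to limit chance imbalance in prognostic factors. The article itself names illness severity as a risk factor for ICU-acquired weakness (Background) and patient heterogeneity as a limitation (Discussion). An unadjusted comparison allows for such imbalance on average, but it does not correct the imbalance that actually occurs, and it leaves in the error term any variance that the baseline data could explain.

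At stake are the width of the confidence interval, the accuracy of the estimate in this one trial, and how clearly its primary result is defined. Recruitment was due to end in February 2016, so the analysis is the remaining place to deal with this.

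**Working it through.** **Inputs from the protocol article.** Difference 54 m, SD 81 m, power 80%, alpha 0.05, 36 per group, raised by 14 to 50 per group (Sample size); significance level 0.05 (Statistical analysis). Two-sided testing is assumed, because it reproduces the stated size.

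**Assumed.** R², the share of 6MWT variance explained by age, sex and APACHE II. The documents give none, so 5, 10, 20 and 30% are shown.

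**Step 1: the plan's own figure.** n per group = 2 × [(1.960 + 0.842) × 81/54]² = 35.3, rounded up to 36. This matches. The exact t-test version gives 36.3. The stated size therefore rests on an unadjusted comparison of means.

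**Step 2: precision at 50 per group.** The residual SD after adjustment is 81 × √(1 − R²), and the standard error of the difference is that SD × √(2/50). Power is from the noncentral t distribution with standardised effect (54/81)/√(1 − R²) and alpha 0.05.

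| Assumed R² | Residual SD (m) | Standard error (m) | Fall in standard error | Power |
|---|---|---|---|---|
| 0 (as planned) | 81.0 | 16.2 | – | 91.0% |
| 5% | 78.9 | 15.8 | 2.5% | 92.3% |
| 10% | 76.8 | 15.4 | 5.1% | 93.6% |
| 20% | 72.4 | 14.5 | 10.6% | 95.8% |
| 30% | 67.8 | 13.6 | 16.3% | 97.6% |

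**Step 3: chance imbalance.** With 50 per group, the difference between arms in a standardised baseline prognostic score has SD √(2/50) = 0.2. An imbalance beyond 0.4 SD, in either direction, is therefore a two-standard-error event with probability about 4.6%. At 0.4 SD the unadjusted 6MWT difference is shifted by √R² × 81 × 0.4:

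- R² = 10%: 0.316 × 32.4 = 10.2 m
- R² = 20%: 0.447 × 32.4 = 14.5 m
- R² = 30%: 0.548 × 32.4 = 17.7 m

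These shifts compare with a target of 54 m.

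**Step 4: does choosing the test by distribution inflate type I error?** The rule was simulated with no true effect, 50 per group and 10,000 runs per distribution: a Shapiro-Wilk test in each arm at 5%, then Mann-Whitney if either rejected and the t test otherwise. The article gives no normality criterion, so this one is an assumption. The rejection rate was 4.8% for normal, 5.2% for skewed and 5.5% for heavy-tailed data. Inflation is not material. Mann-Whitney was chosen in about 9%, nearly 100% and 59% of runs respectively, so which effect measure is tested depends heavily on the shape of the data.

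**The case against.** **The planned test is valid.** After 1:1 randomisation the unadjusted comparison is unbiased, and its overall type I error already allows for chance imbalance. This stands. A reader might infer that simple randomisation without adjustment biases the trial or invalidates its p values; neither the documents nor the calculation supports that.

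**The choice of test follows a rule.** The switch depends on the shape of the data and not on which test gives the smaller p value. This also stands. A reader might infer a search for significance, but the text describes none, and step 4 shows no material inflation. What remains is that the rule leaves the effect measure open.

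**An unseen analysis plan may add detail.** Covariate lists and a normality criterion are often left to it, and the article does not exclude an adjusted analysis. That would answer a complaint about silence. Here, however, the article states which comparison is to be made, and the point concerns that stated choice.

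**The gain may be small.** No baseline 6MWT is possible in ventilated patients. The article links severity to the development of weakness, and gives no figure for how far age or severity predicts walking distance among those discharged. At R² = 5% the gain is 1.3 percentage points of power, from a base that is already adequate. This limits the size of the point.

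**Unequal arm sizes.** Simple randomisation can also produce uneven groups, but a 40:60 split of 100 lowers power only from 91.5% to 90.4% (normal approximation), and covariate adjustment would not cure it. It forms no part of the case.

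**Conclusion.** The point holds as an improvement in efficiency and prespecification. It is not an error in the plan. The stated primary comparison does not fix whether a mean difference or a rank comparison is estimated, and it leaves aside baseline data already collected.

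At 50 per group and alpha 0.05, adjustment would add 1.3 to 6.6 percentage points of power and reduce the standard error by 2.5 to 16% for R² between 5 and 30%. A 0.4 SD imbalance, uncommon at about 4.6% in either direction, would move the unadjusted 6MWT difference by about 10 to 18 m for R² of 10 to 30%.

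These sizes rest on the assumed R², on the protocol's SD of 81 m and on 50 analysed patients per group. They concern the 6MWT only, as the article gives no planning figures for the FIM. That the effect measure is left open follows from the text and needs none of these assumptions.

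**What to change.** Before outcomes are seen by arm, name one primary method for each primary outcome, to be used whatever the observed distribution: a linear model with arm, age, sex and admission APACHE II, reporting the adjusted mean difference with its 95% confidence interval. State that robust or bootstrap standard errors will be used if residuals are skewed, so that the effect measure does not change. Use only covariates measured before treatment; the daily SOFA scores and medication recorded after allocation do not qualify. Keep the unadjusted t test and Mann-Whitney as sensitivity analyses.

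The cost is a few sentences of analysis-plan wording, slightly more analysis work and a few degrees of freedom. The covariates are already collected, so no patients and no new data are needed, and the randomisation is untouched.

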## Discussion

This prospective, single-centre, allocation-concealed and assessor-blinded randomised controlled trial with 6-month follow-up will be the first, to our knowledge, to evaluate both an early endurance and resistance training compared to standard care in the mechanically ventilated, critically ill patient from a general ICU population. Considering the devastating consequences of ICUAW, it is imperative to find interventions that improve function and thereby quality of life. The two chosen primary outcomes, 6MWT and FIM, reflect these important physical impairments of ICUAW, and thus have a high clinical relevance for patients surviving prolonged mechanical ventilation. Therefore, the strengths of this trial lie in the pragmatic design of the early initiation and physiotherapy-driven protocol, the prospective inclusion of patients at risk of prolonged mechanical ventilation and its consequences in the form of ICUAW in a wide general ICU population that will be screened for study recruitment within 12 h after ICU admission and will, therefore, be enrolled very early into the trial, as well as the everyday significance of the chosen outcome measure to the participants up to 6 months after hospital discharge. If the experimental intervention should prove superior to standard care, it will be relatively simple to incorporate the intervention protocol into daily routine so that it can be used elsewhere or for guideline development. Limitations of this study are the heterogeneity of the critically ill and the discontinuity of the protocol after relocation to the other wards within the hospital. Also, due to the trial’s nature, it is impossible to blind the treating physiotherapists, ICU staff and the participants to the intervention. However, the outcome assessors will be blinded to group allocation. Finally, the reporting of adverse events during therapy will depend on the treating physiotherapists, which could lead to missing events. However, physiotherapists have been carefully trained and work closely with the ICU nurse at the bedside. Moreover, all safety parameters will be continuously recorded by the PDMS for further safety analysis.

